## Abstract

**Background:**

Hospitalisation rates for the older population have been increasing with end-of-life care becoming a more medicalised and costly experience. There is evidence that some of these patients received non-beneficial treatment during their final hospitalisation with a third of the non-beneficial treatment duration spent in intensive care units. This study aims to increase appropriate care and treatment decisions and pathways for older patients at the end of life in Australia. This study will implement and evaluate a prospective feedback loop and tailored clinical response intervention at three hospitals in Queensland, Australia.

**Methods:**

A stepped-wedge cluster randomised trial will be conducted with up to 21 clinical teams in three acute hospitals over 70 weeks. The study involves clinical teams providing care to patients aged 75 years or older, who are prospectively identified to be at risk of non-beneficial treatment using two validated tools for detecting death and deterioration risks. The intervention’s feedback loop will provide the teams with a summary of these patients’ risk profiles as a stimulus for a tailored clinical response in the intervention phase. The Consolidated Framework for Implementation Research will be used to inform the intervention’s implementation and process evaluation. The study will determine the impact of the intervention on patient outcomes related to appropriate care and treatment at the end of life in hospitals, as well as the associated healthcare resource use and costs. The primary outcome is the proportion of patients who are admitted to intensive care units. A process evaluation will be carried out to assess the implementation, mechanisms of impact, and contextual barriers and enablers of the intervention.

**Discussion:**

This intervention is expected to have a positive impact on the care of older patients near the end of life, specifically to improve clinical decision-making about treatment pathways and what constitutes appropriate care for these patients. These will reduce the incidence of non-beneficial treatment, and improve the efficiency of hospital resources and quality of care. The process evaluation results will be useful to inform subsequent intervention implementation at other hospitals.

**Trial registration:**

Australia New Zealand Clinical Trial Registry (ANZCTR), ACTRN12619000675123p (approved 6 May 2019),

## Background

The older population is increasing worldwide as a result of longer life expectancy and lowered fertility rates [1]. Older persons typically have increased frailty, chronic health conditions and multiple morbidities [2, 3]. While health care use and expenditure in this population is variable, health care expenditure is markedly higher at the end of life [2, 4].

There are challenges to caring for this older population in acute care settings. Specifically, clinicians, patients and families grapple with tensions between the limits of medicine, subjective judgements about beneficence, and economic and clinical imperatives to provide appropriate and quality patient care [5]. Clinicians providing end-of-life care, who are often tasked with preparing patients and families for a transition to palliative and supportive care pathway [6], frequently experience barriers to these discussions [7, 8]. This leads to an increase in non-beneficial treatment, causes moral distress to clinicians, and prolongs or increases patient suffering [9]. A systematic review of 38 international studies found 33 to 38% of patients received non-beneficial treatment at the end of life [10].

These barriers have been broadly categorised as arising from clinician factors, hospital factors and patient factors [7, 11–14]. Addressing these factors is challenging, especially in large, complex acute care settings. Evidence exists for interventions to reduce non-beneficial treatment outside of acute hospitals [15–18], and an intervention study has been done in the Intensive Care Unit (ICU) setting in the United States [19]. There is no published research in Australia evaluating an intervention to reduce non-beneficial treatment at the end of life in hospitals.

As with other developed countries, Australia’s health care system faces urgent challenges from an ageing population. This population is more likely to be hospitalised than in the past, with hospitalisation rates for people aged over 85 years increasing by 35% for women and 48% for men in the decade to 2011 [20]. The end-of-life phase in Australia is becoming an increasingly medicalised experience with 54% of deaths occurring in hospital [21]. A retrospective study [22] of three Australian hospitals in 2012 identified 12.1% (range 6.0 to 19.3%) of end-of-life admissions received non-beneficial treatment. These admissions received non-beneficial treatment for an average of 15 days including 5 days spent in the ICU. This same study estimated an annual national health system cost of $A153 million due to non-beneficial bed days.

The Intervention for Appropriate Care and Treatment (InterACT) study will implement a prospective, tailored feedback loop intervention in three acute hospitals in Queensland, Australia. We will evaluate whether the intervention improves care outcomes for older patients, specifically to increase appropriate care and treatment pathways, and reduce the incidence of non-beneficial treatments. This study will use two validated tools concurrently to prospectively identify patients at the end of life where curative and life-sustaining interventions may be non-beneficial. The Criteria for Screening and Triaging to Appropriate aLternative Care (CriSTAL) tool was developed to identify elderly patients in the last months of life [23–25]. The Supportive and Palliative Care Indicators Tool (SPICT™) can be used to identify patients at risk of deteriorating and dying [26] with recent studies reporting an association between a SPICT-positive result and one-year mortality [27, 28].

Patient screening with both tools will be the first step in the prospective feedback loop intervention. Providing feedback to clinical teams aims to increase clinician awareness of their patients’ risk profile, directly addressing some of the known clinician and hospital factors for non-beneficial treatment [29–31]. A tailored clinical response to this information will be determined and implemented by the clinical teams, with support from a hospital executive advisory group.

The primary objective of the study is to determine the impact of a tailored clinical team feedback loop intervention on outcomes related to appropriate care and treatment at the end of life. The extent of change in health service use and costs will also be estimated. A second objective is to conduct a process evaluation to assess implementation, mechanisms of impact, and contextual barriers and enablers of the feedback loop intervention.

## Methods/design

### Study design

This is a randomised controlled trial using a multi-centre stepped-wedge randomised design (Fig. 1). Five stages will be sequentially rolled-out across the three hospitals over 70 weeks: site preparation; usual care exposure; intervention establishment; intervention exposure; and post-intervention. The timing of the one-way crossover from usual care to intervention establishment will be randomly allocated.

**Fig. 1 Fig1:**
[figure not shown]
Stepped-wedge study design in three hospitals with seven teams per hospital for the InterACT trial

### Study setting and population

This trial will be undertaken at three large, acute Queensland teaching hospitals. We will aim to enrol seven clinical teams at each hospital. In consultation with the local hospitals’ executive advisory group, we will purposively sample from acute-care clinical teams and medically-oriented clinical specialities that have a regular number of patient admissions ≥75 years. This supports trialling the intervention in clinical teams that routinely have an older patient population who are more likely to receive non-beneficial treatment.

For inclusion, clinical teams must:
be an established clinical team unit or specialty that routinely admits patients within the hospitalinclude at least one nominated lead specialist consultantinclude at least one registrar and affiliated clinical nurse consultant or nurse unit managerhave a clinical team structure and admission pattern typical of the hospitalhave a consistent history of admitting patients aged 75 years or over during the previous yearparticipate in an information session with the project team.

Excluded clinical teams will additionally include those already implementing interventions or initiatives related to reducing non-beneficial treatments for older patients, and those from the emergency department, any Intensive Care Units (ICUs), mental health units, and non-acute care. The excluded specialities likely have different clinical and treatment focus which would require a different implementation plan.

At each hospital, enrolled clinical teams, executive advisory group members and site study team members will be recruited for the process evaluation. Site study team members will include hospital employees who have a role in supporting the implementation of the trial or in data collection, as determined in the site preparation phase, and may include the nurse auditor, site coordinator, and palliative care team.

### Intervention

The study intervention (InterACT) is a prospective feedback loop to clinical teams with tailored clinical response, based on the outcomes of a patient record review (or screening) process using the CriSTAL and SPICT tools. The intervention process is shown in Fig. 2.

**Fig. 2 Fig2:**
[figure not shown]
Schematic of the InterACT intervention to be implemented

For the purpose of this study, patients are considered to be in the at-risk population if they were identified to be *high-risk CriSTAL* and *SPICT-positive*. Patients are classified as *high-risk CriSTAL* (at high risk of death within 3 months) if they have a CriSTAL score of 6 or greater. Patients with a SPICT general indicator score of 2 or greater are considered *SPICT-positive* (presence of indicators of potential deterioration within 12 months).

Site based trained auditors will review patient records of new admissions to participating clinical team twice weekly to identify patients in the at-risk population. Record review data will be collected using an electronic form in REDCap [32].

### The feedback loop

In the intervention exposure phase, the study team will provide feedback based on the record review results to individual clinical team nominees after each screening episode. The study team will develop computer scripts to automate the processes of exporting the data from REDCap into R [33], processing the data and generating the feedback report. The project manager will provide the feedback report to clinical team nominees in an agreed format. The feedback report process includes email, text or database log-in (or a combination of).

This feedback is intended to flag that a patient is in the at-risk population, and to act as a stimulus to review patient care activities and pathways [30, 34]. Clinician expertise and autonomy will not be questioned in the feedback, nor will judgements be made about the likelihood of non-beneficial treatment. Examples of potential clinician response to the feedback include palliative care referral, multidisciplinary team review, advance care planning consultation, and patient/family meetings.

### Implementation framework

We will use the Consolidated Framework for Implementation Research (CFIR) [35] to inform the implementation and process evaluation of the InterACT study intervention. The intervention will be fully described in a CFIR-based implementation toolkit that identifies what parts of the feedback loop intervention will be fixed, what will be flexible, and the associated degree of flexibility.

The toolkit will support the local tailoring of the intervention to reflect hospital context, clinical team structure and workflows. The project team, study team, hospital executive advisory group and enrolled clinical teams will collaboratively develop and pilot an effective feedback loop and associated clinical team response during the intervention establishment phase.

### Monitoring and evaluating implementation

Process evaluation is an essential part of designing and testing complex interventions [36]. The real-world setting and length of this trial will require a pragmatic approach to fostering intervention adherence, reach and fidelity. The project team will systematically monitor the implementation process as part of the process evaluation using templates and approaches based on the CFIR constructs. This embedded approach will provide direct support for implementing the InterACT study intervention and will inform understanding of how the implementation process contributes to the study outcomes.

### Study outcomes

The study outcomes and outcome measures are described in Table 1. Outcomes 1 to 9 are for patients admitted under the enrolled clinical teams and identified to be in the at-risk population following screening with the CriSTAL tool and SPICT. The measurement tools used are summarised online [37].

**Table 1 Tab1:** Project outcomes and outcome measures for the InterACT study

Outcome label	Outcome	Outcome measure
**Impact outcomes**		
Primary outcome (Outcome 1)	Proportion of patients with one or more Intensive Care Unit (ICU) admissions	ICU admissions during the current hospital stay from the date first recorded as *high-risk CriSTAL and SPICT-positive*.
Outcome 2	Length of hospital stay and discharge outcome	Length of hospital stay, with the transition endpoints of ‘discharged alive’ and ‘death in hospital’, from the date first recorded as *high-risk CriSTAL and SPICT-positive.*
Outcome 3	Time to hospital re-admission	The time in days to re-admission to any Queensland public hospital for re-admissions within 12 weeks from the date of discharge.
Outcome 4	Time to first documented indications of clinician-led care review discussion	The time in days from the date first recorded as *high-risk CriSTAL and SPICT-positive* to documentation of a clinician-led care review activity. The type of care review activity (reduce/cease active treatment, increase comfort care, continue active treatment) and indications of family conflict will also be recorded.
Outcome 5	Time to first care directive measure	The time in days from the date first recorded as *high-risk CriSTAL and SPICT-positive* to documentation of any care directive (including discussion outcomes, advance care plan, statement of choices, acute resuscitation plan). The type of care directive will also be recorded.
Outcome 6	Time to first palliative care referral	The time in days to first documented palliative care referral from the date first recorded as *high-risk CriSTAL and SPICT-positive* during the current hospital stay.
Outcome 7	Time to first medical emergency call	The time in days to first medical emergency call during the current hospital stay.
**Health care resource use and cost outcomes**		
Outcome 8	Changes in admission/hospitalisation and treatment costs	Costs of treatment will be taken from routinely collected information and will begin accumulating from the date first recorded as *high-risk CriSTAL and SPICT positive*. This ensures that treatment costs reflect only those costs that relate to care provided at the end-of-life phase. All costs will be stratified by the acute and palliative care phases so that any changes resulting from different treatment pathways can be identified.
Outcome 9	Cost of implementing the prospective feedback loop intervention	The cost of implementing the study intervention will be measured by the duration and unit costs of staff time associated with completing direct trial activities (including document review and clinical team feedback activities).
**Process outcomes**		
Extent and fidelity of intervention implementation, impact, and contextual barriers and enablers of the feedback loop intervention		

We chose ICU admissions as the primary outcome as the at-risk population is less likely to benefit from ICU admission, and it is a commonly used proxy for non-beneficial treatment in hospital [10]. That said, this is a complex trial and the overall impact of the intervention will be more appropriately represented through consideration of all outcomes listed.

### Study procedures

#### Recruitment, enrolment and withdrawal

The project manager will invite eligible clinical teams to participate at routine meetings in the hospitals during the recruitment period. The project manager, an executive sponsor and site-based study coordinator will explain the study and what is involved. All interested clinicians will have access to the participant information sheets and full study protocol [37].

Clinical teams will be enrolled by the project manager. A nominated lead clinician will provide agreement on behalf of their clinical team. As the unit of enrolment is the clinical team, if an individual clinician participant, including the lead clinician, withdraws from the study, data collection and clinical team participation will continue unchanged.

Once enrolled, clinical team participation will only be discontinued if ongoing participation is untenable or negatively impacting patient care. The trial will only be discontinued if a regulatory body, funding body, or ethics committee judges it necessary for medical, safety, regulatory, or other reasons consistent with applicable laws, regulations and good clinical practice.

#### Randomisation, allocation and blinding

All three hospitals will receive the intervention, with the timing randomised. A statistician investigator ([name]) will be responsible for computer generation of the trial timing randomisation as per Fig. 1 and the intra-hospital clinical team identifiers. These identifiers will help anonymise the data storage and reporting.

Given the nature of the intervention and trial design, it is not possible to blind the clinical teams to the intervention. The intervention exposure phase commencement date will be concealed from the hospital teams during the site preparation and clinical team recruitment phase. Hospital teams will be notified of their intervention establishment and intervention exposure start dates about 8 weeks prior to allow time to plan for the intervention establishment phase activities.

#### Data collection

Site-based trained nurse auditors will prospectively collect identifiable patient data during record screening using an online form in REDCap. The auditors will review patient records of all new admissions to participating clinical teams twice weekly to identify patients in the at-risk population. At-risk patients will be passively monitored at subsequent screening times if they have not been discharged or transferred to a different facility. Auditors will record if and when these patients had documented indications of clinician-led care review discussion, care directive measures, and palliative care referral. Data custodians will link outcome data for patients at the end of the intervention exposure period.

Members of the clinical team and the site-based study team will be asked to complete monitoring documents, including capturing time spent on intervention activities, to assess adherence to and fidelity of the intervention.

Process evaluation data will be collected using templates based on the CFIR. Clinical team members will be invited to participate in group or individual interviews after the pilot in the intervention establishment phase, during the intervention exposure phase, and during the post-intervention phase. The hospital advisory group and site-based study teams will also be asked to voluntarily participate in a group or individual interview about the implementation process during the post-intervention phase.

Additional details on the data items, collection methods and schedule, and data management are provided online [37].

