#### Analyses of secondary outcomes

Competing-risk proportional hazards survival models will be used to analyse time-to-event outcomes during patient hospitalisations (outcomes 2, 4, 5, 6 and 7). Hospital discharge and in-hospital deaths are treated as competing risks. Use of the competing risk survival model provides an estimate of the intervention effect which appropriately accounts for the competing and time-varying nature of discharge and death on the outcomes [41]. The models will have a binary variable indicating if patients were in the intervention exposure phase. The survival analysis will adjust for likely predictors of patient age, sex and time spent in hospital for identified hospital episode prior to admission to enrolled clinical team. The survival analysis will stratify by clinical teams to control for consistent differences between teams. Cumulative incidence curves will be used to compare the event rates over time between the usual care exposure and intervention exposure phases.

We will use a proportional hazards survival model to investigate the difference between usual care and intervention exposure phases in the time to re-admission within the first 12 weeks after index discharge (outcome 3). Patients who died after leaving hospital or were not re-admitted within the 12 weeks will be censored. Clinical teams will be included as strata.

Data on the health services used by patients during their hospital admission will be retrieved from the hospitals’ clinical costing database to evaluate changes in admission and treatment costs (outcome 8). Any costs that occurred before the patient was identified to be in the at-risk population will be excluded. Statistical distributions will be fitted to describe variability in all cost parameters. The key measure of cost will be the average cost per patient. This will be presented alongside 95% bootstrap confidence intervals to estimate the uncertainty in this average.

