### Study status

The protocol version is 6.0 (28 January 2020), which has been adapted to suit the formatting requirements of the journal. The trial is prospectively registered with the Australia New Zealand Clinical Trial Registry (ANZCTR), ACTRN12619000675123p (Registration date: 6 May 2019).

All ethical and governance approvals are in place at each of the participating hospitals. The trial component started recruitment in February 2020, with an expected end date of August 2021.

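### As written, linking outcome data at the end of exposure cannot supply Outcome 3's 12-week re-admission window for late intervention-phase patients

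*Protocol article*

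**What the plan says.** Data collection fixes when outcomes are linked: "Data custodians will link outcome data for patients at the end of the intervention exposure period". In the same section, the auditors' passive monitoring of at-risk patients ends at discharge or transfer to another facility.

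Table 1 defines Outcome 3 as: "The time in days to re-admission to any Queensland public hospital for re-admissions within 12 weeks from the date of discharge".

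Analyses of secondary outcomes names the model: "We will use a proportional hazards survival model to investigate the difference between usual care and intervention exposure phases in the time to re-admission". It gives one censoring rule: "Patients who died after leaving hospital or were not re-admitted within the 12 weeks will be censored". It gives no rule for a patient with fewer than 12 weeks of observed follow-up at linkage.

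Study design lists the stages as "site preparation; usual care exposure; intervention establishment; intervention exposure; and post-intervention", with a one-way crossover from usual care. The lengths of the exposure and post-intervention stages are not in the text.

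**The concern.** Re-admission to any Queensland public hospital is only visible through linked data, because the auditors stop following a patient at discharge. If the extract is taken when exposure ends, a patient discharged three weeks before that date has three weeks of re-admission data, not twelve.

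The shortfall is one-sided. Because the crossover is one-way, the patients at the end of data collection are intervention-phase patients. Usual-care patients were discharged earlier, with establishment and exposure still to come.

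At the least, intervention-phase events are lost. At worst, unobserved weeks are counted as event-free weeks in one phase only, and a neutral result on re-admission looks like a benefit. This matters because the Study outcomes section says the overall impact is better judged from all the listed outcomes than from the primary outcome alone.

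**Working it through.** The article gives no figure for Outcome 3, so there is none to reproduce.

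**Inputs.** From the article: a 12-week window, linkage at the end of exposure, and a proportional hazards model. Assumed, because the text does not give them: exposure length L per hospital (20, 26 or 39 weeks), 12-week re-admission risk of 30% or 50%, discharges uniform over exposure, each hospital's data ending on its last exposure day, and no true effect (hazard ratio 1).

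**Step 1: who is affected.** The share of intervention-phase discharges in the last 12 weeks is 12/L. These patients have on average 6 of their 12 weeks available. The share of planned follow-up time that is available is therefore 1 − (12/L)(6/12) = 1 − 6/L.

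**Step 2: events lost.** Take a constant hazard and a 30% risk. The cumulative hazard over 12 weeks is −ln(0.70) = 0.357. The mean observed risk in the late group is 1 − 0.30/0.357 = 15.9%. At L = 26 the intervention phase would show 0.46 × 15.9% + 0.54 × 30% = 23.5%. That is 23.5/30 = 0.78 of its events, or about 22% lost. The same sum gives about 28% lost at L = 20 and 14% at L = 39.

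**Step 3: effect on the hazard ratio.** I simulated 60,000 patients per phase with a true hazard ratio of 1. Usual care was followed for the full 84 days and the intervention phase was cut off at the end of exposure. A Cox model was fitted under two codings of patients who were not fully followed. Ranges cover the 30% and 50% risks under a constant hazard.

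| L (weeks, assumed) | Share affected, 12/L | Follow-up available, 1 − 6/L | HR if censored at extract date | HR if censored at day 84 |
|---|---|---|---|---|
| 20 | 60% | 0.70 | 0.99–1.01 | 0.69–0.70 |
| 26 | 46% | 0.77 | 1.00–1.02 | 0.76–0.78 |
| 39 | 31% | 0.85 | 0.99–1.00 | 0.83–0.84 |

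The last column tracks 1 − 6/L, as it should: events come from that fraction of the time, but nearly the full time is counted. With a decreasing hazard (Weibull, shape 0.6), day-84 coding gives about 0.78, 0.82–0.83 and 0.87–0.88 for the three values of L. Censoring at the extract date again gives 0.98–1.00.

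**Step 4: does the calendar settle it?** Study status says: "The trial component started recruitment in February 2020, with an expected end date of August 2021". If the 70 weeks start in February 2020, they end between 5 June and 3 July 2021, about 4 to 12 weeks before the possible end dates in August 2021. The post-intervention stage lies inside the 70 weeks and its length is not in the text. The dates therefore neither show nor exclude a full 12 weeks after exposure.

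**The case against.** A reader might infer that the intervention will look better on re-admission than it is. The article does not support that. Outcome 3 is analysed as a time to event, not as the proportion re-admitted by week 12. Unequal administrative follow-up is what censoring handles, and the simulation confirms it: 0.98 to 1.02 when the truth is 1. The biased hazard ratios need a coding step that the article does not state. Censoring at last observation is the ordinary default. Comparing the crude proportions from Step 2 between phases would also mislead, but that comparison is not planned. All of this stands.

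It can also be said that the linkage sentence only places linkage after exposure and does not set a data cut-off on the last day. A post-intervention stage follows, and the article refers to the online protocol for the collection schedule. This stands in part. Linkage may well run later in practice, and a single extract for hospitals finishing on different dates would give the earlier finishers more follow-up than 12/L implies. But the article does state a time, ties it to the end of exposure rather than to the later stage, and does not reconcile it with the 12-week window.

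Nor does the 12-week problem reach the primary outcome, since ICU admission is counted within the current stay only. Length of stay is analysed with survival models that can censor patients still in hospital. Incomplete stays and costs at linkage are a smaller issue, which the article's figures do not allow me to size.

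**Conclusion.** The stated linkage time and the 12-week window of Outcome 3 conflict on a literal reading, and the shortfall would fall on the intervention phase. Under the assumed exposure lengths of 39 down to 20 weeks, 31% to 60% of intervention-phase discharges would be incompletely followed.

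The consequence depends on coding. With censoring at the extract date there is essentially no bias in the hazard ratio, only lost events and precision. With day-84 coding, the hazard ratio would be about 0.7 to 0.85 under a constant hazard with no true effect, and somewhat nearer 1 if the hazard falls over time. The censoring sentence leaves the second coding open but does not prescribe it.

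These figures rest on assumed exposure lengths and re-admission risks, uniform discharge, and a simple two-group simulation without the planned stratification by team. The 12-week problem concerns one secondary outcome. It is worth correcting because the change is small and closes a route to one-sided bias.

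**What to change.** In Data collection, set the linkage extract at least 12 weeks after the last index discharge in the last hospital to finish, plus the custodians' coding lag. In Analyses of secondary outcomes, add that anyone with fewer than 12 weeks of observed follow-up is censored at the extract date, not at 12 weeks.

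The first change gives every patient the full 84-day window and recovers the lost intervention-phase events. The second protects the hazard ratio if the extract has to be taken early. The cost is one changed date in the data request, one added sentence, and final data about three months later. If the full protocol already sets a later extract, it is enough to bring the article's sentence into line with it.
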